### Procedure for handling missing data

2.6.

Statistical analysis will involve intention-to-treat analysis. In the occurrence of missing data during the study, the statistical analysis will be performed by carrying forward data from the previous observation to adjust for the missing data in the assessments after the intervention.

### Data management

2.7.

All data will be stored for three years after the conclusion of the study in an online databank. All electronic files related to the study will only be accessible to key personnel and all computers will be protected by passwords. Each participant will receive an exclusive identifier upon inclusion to the study that will be used for all documentation related to the study. The forms and files in print will be kept in a cabinet by the coordinator of the study locked in a secure office.

### Trial status

2.8.

Recruitment of the participants began in January 2023 and should end in December 2023. The conclusion of the study is predicted for March 2024.

### Expected results

2.9.

We believe that the three intervention groups will exhibit improvements in motor skills, mobility and functional balance directly related to gait and balance training. However, the effect size is expected to be larger in the experimental groups involving motor training combined with active tDCS (motor cortex and cerebellum) compared to the control group (sham tDCS) with regards to the motor outcomes. We also expect the effects obtained in the experimental groups to be maintained at the follow-up evaluations four and eight weeks after the end of the interventions. Lastly, we expect the motor effects to result in an improvement in the global performance of the children with ASD who participate in the study, including cognitive and behavioral aspects assessed using ADOS and CARS.

## Discussion

3.

Motor training combined with tDCS has been shown to be safe, viable and effective for children and adolescents with motor control disorders. Considering the results available in the scientific literature demonstrating the promising effects of anodal tDCS in children with ASD, especially aspects related to communication and behavior, it is of interest to expand the knowledge regarding the effects of tDCS also on motor skills in this population. If demonstrated that anodal tDCS administered over areas of the brain involved in motor control, such as the primary motor cortex and cerebellum, can enhance the effects of gait and balance training in only ten sessions in two consecutive weeks, the clinical applicability of this stimulation modality will be expanded as well as more scientifically founded.

Although abnormalities in gait and balance are not primary characteristics of ASD, such abnormalities compromise independence and global functioning during the execution of routine activities of childhood. Motor rehabilitation poses a challenge for therapists, families and patients, as children with ASD are often enrolled in behavioral treatment programs that require a considerable number of intervention hours per day. Thus, therapeutic possibilities with execution in focused, short-term programs that prove effective could be a favorable option for the treatment of abnormalities in motor skills.

Therefore, the present protocol for a randomized controlled clinical trial involves assessment measures of results with representativeness in the daily activities of children. Motor skills will be assessed using the MABC-2, which consists of items that measure gross and fine motor skills, to determine whether motor training (gait and balance) combined with anodal tDCS achieves positive results not restricted to the motor task being trained. Scales and tests will be used to measure the effects on mobility and balance during functional activities, such as walking, standing up, sitting down, changing direction, etc. These assessment tools will enable the understanding of the effects on an important domain of the International Classification of Functioning, Disability and Health – ACTIVITY, which is the primary focus of the proposed intervention.

The results of the clinical trial will also enable a better understanding of the effects of tDCS considering the specificity of the areas of the brain stimulated (primary motor cortex and cerebellum). Studies as that proposed in this protocol can also contribute to better decision making in terms of the “ideal target area” for the administration of tDCS in accordance with the clinical objective and proposed training.

Moreover, the proposed study involves the determination of the motor evoked potential, which is a measure of cortical excitability for the assessment of brain structure and function, enabling the analysis of whether a neurophysiological change in this parameter will be related to the results obtained in aspects related to motor skills – gait and balance. Lastly, the assessment of cognitive and behavioral aspects using the ADOS and CARS measures will enable understanding whether the intervention has an impact on the symptoms and intensity of the symptoms of ASD as well as indirectly enable measuring the effects of the intervention on the child’s participation, as these assessment measures involve the perceptions of family members with regards to the child’s performance and participation in routine activities.

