**Methods and design:**

A randomized, sham-controlled, double-blind clinical trial will be conducted involving 30 children with ASD that will be recruited to receive ten sessions of sham or ten sessions of active anodal tDCS (1 mA, 20 min) over the primary motor cortex or cerebellun combined with motor training. The participants will be assessed before as well as one, four and eight weeks after the interventions. The primary outcome will be gross and fine motor skills. The secondary outcomes will be mobility, functional balance, motor cortical excitability, cognitive aspects and behavioral aspects.

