As a resource considered safe, inexpensive and easy to administer, tDCS could contribute to the rehabilitation of these children, as its neurophysiological effects have been demonstrated to favor the learning of new voluntary motor and postural control strategies. Considering the complexity of brain activity dysfunctions observed in ASD, we need to investigate whether anodal tDCS may (or may not) contribute to motor training results. In addition, it is necessary to understand what are the effects of facilitating cortical excitability of fundamental structures of motor control, such as, for example, the primary motor cortex and the cerebellum. This information may benefit future clinical indications of tDCS for rehabilitation of children with ASD. However, the scientific literature is extremely limited regarding the effects of tDCS on areas of motor control in children with ASD.

The main goal of the present study is to compare the effects of ten 20-min sessions of neurofunctional motor training combined with anodal tDCS over the primary motor cortex, cerebellar region and sham stimulation on motor ability in children with ASD. Specifically, the aim is to determine whether anodal tDCS over these areas of the brain can optimize the effects of gait and postural control training on gross and fine motor skills, mobility, functional balance, motor cortical excitability, cognitive aspects and behavioral aspects in children with ASD. Our central hypothesis is that all individuals will present functional improvements following gait and balance training, but the benefits will be more evident after the administration of active tDCS (primary motor cortex and cerebellar region) compared to the group receiving sham tDCS due to the neurophysiological effects on cortical excitability. Moreover, we believe that the effects of anodal tDCS over the primary motor cortex will be restricted to motor outcomes, whereas the effects of anodal stimulation over the cerebellar region will also be found in outcomes related to cognitive and behavioral aspects.

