### Assessment measures

2.3.

The study will involve assessment tools used for the diagnosis and classification of the severity of ASD, with the measurement of cognitive and behavioral aspects, an assessment tool for gross and fine motor skills (primary outcome), a functional mobility test, a test for the assessment of spatiotemporal gait variables, a functional balance scale, a neurophysiological assessment of motor cortical excitability (evoked motor potential) and a questionnaire addressing side effects. In addition, informations about the medications will be collected, including the name of the medication, dosage and frequency of use, and how long the child has been using the medication. The order of evaluations will be random, through simple randomization carried out by draw.

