#### Assessment tools and categorization of groups according to ASD

2.3.1.

The Autism Diagnostic Observation Schedule (ADOS) will be used to confirm the diagnosis of ASD and to assess the behavior of the children in terms of particular structured activities. The ADOS is composed of four modules, all with good reliability, sensitivity and specificity for ASD (64, 65). Each module is designed for individuals with specific degrees of linguistic development and involves a protocol of structured, dynamic interactive activities conducted by a trained examiner in a period of approximately 45 min. The aim of the different tasks is to provide information on social behavior, communication and general aspects of the individual being assessed. Based on observations on how the individual performs the tasks, the therapist answers a questionnaire, attributing scores for the different behaviors. The questions are organized on a four-point scale, with 0 indicating no abnormality and 3 indicating moderate to severe abnormalities (66). To be classified as an individual with autism or ASD according to the ADOS, the sum of the scores defined in the algorithms of the four modules must reach minimum cutoff points in the domains referring to communication and reciprocal social interaction (67, 68). The ADOS is an ASD diagnostic instrument, but we also chose to use it in post-intervention assessments, with the intention of identifying possible changes in the participants’ performance during the execution of tasks.

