The Brazilian version of the Childhood Autism Rating Scale (CARS-BR) will be administered to the parents or guardians for the classification of the severity of ASD. CARS-BR is an observation scale with 15 items to assist in the identification of children with ASD and distinguish children with impaired development without autism as well as distinguish autistic children with intellectual disability. Its importance consists of the differentiation of mild to moderate autism from severe autism. The scale is short and appropriate for use on any child older than two years of age. The scale was validated for Brazilian Portuguese in a study conducted for 15 years involving 1,500 children with autism (62). The scale assessed behavior in 14 domains generally affected by autism plus a general autism impression category. The scores of each domain range from 1 (within the limits of normality) to 4 (severe autistic symptoms). The overall score ranges from 0 (no characteristics of autism) to 60 (all severe characteristics met). Its use offers several advantages over other instruments, such as the inclusion of items that represent varied diagnostic criteria and reflect the actual dimension of the disorder, applicability to children of all ages (including preschoolers) and objective, quantifiable scores based on direct observation (62).

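### Cognition is a named outcome and part of the cerebellar hypothesis, but only ADOS and CARS-BR are assigned to it, so a change in those scores cannot be reported as a cognitive effect

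*Protocol article*

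**What the plan says.** The Abstract (Methods and design) states: "The secondary outcomes will be mobility, functional balance, motor cortical excitability, cognitive aspects and behavioral aspects". The specific aim in the Introduction (section 1) covers "gross and fine motor skills, mobility, functional balance, motor cortical excitability, cognitive aspects and behavioral aspects in children with ASD", and the visit list in section 2.1 names the same two aspects at baseline and at the four- and eight-week follow-ups.

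The Introduction then states a hypothesis about stimulation site. It expects that "the effects of anodal tDCS over the primary motor cortex will be restricted to motor outcomes". For cerebellar stimulation it expects benefit on the cognitive and behavioural side as well.

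On measurement, section 2.3 announces "assessment tools used for the diagnosis and classification of the severity of ASD, with the measurement of cognitive and behavioral aspects". Section 2.9 (Expected results) names the tools as ADOS and CARS, and the Discussion (section 3) again refers to "the assessment of cognitive and behavioral aspects using the ADOS and CARS measures".

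Section 2.3.1 describes the two instruments. Of ADOS it says: "The aim of the different tasks is to provide information on social behavior, communication and general aspects of the individual being assessed". It also calls ADOS a diagnostic instrument that the authors chose to repeat after the intervention. CARS-BR "will be administered to the parents or guardians for the classification of the severity of ASD"; it rates behaviour in 14 domains plus a general impression and yields an overall score.

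**The concern.** A construct named as an outcome needs a measure of that construct. Here cognition appears in the aim, in the outcome list and in a hypothesis meant to distinguish the two active arms, but the instruments given for it are described as measuring something else. If the plan is followed as written, a lower ADOS or CARS-BR score in the cerebellar arm would be reported as support for a cognitive benefit when what was observed is a change in autism symptoms. The Discussion intends the results to inform the choice of target area for stimulation, so such a claim could carry weight beyond this trial.

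The site hypothesis raises a second, smaller issue. One half of it predicts an effect in one arm and the other half predicts none in another arm. It is easily, and wrongly, judged by setting a significant result in one arm beside a non-significant result in the other.

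**Working it through.** The main point is one of construct and measurement, and the plan gives no figure to reproduce. The check matches each stated construct to its instruments.

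**Step 1. Which instruments are assigned to cognition?**

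| Place | What it assigns |
|---|---|
| Section 2.3 | Cognitive and behavioural aspects are attached to the diagnosis and severity tools; no separate cognitive test is in the list |
| Section 2.9 | ADOS and CARS |
| Section 3 | ADOS and CARS |
| Captions of Figures 1 and 2 | No other candidate among the abbreviations (MABC-2, PBS, TUG, MEP, ADOS, CARS) |

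**Step 2. What does the protocol say these instruments measure?**

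| Instrument | Described purpose and content (section 2.3.1) | Cognitive score defined? |
|---|---|---|
| ADOS | Confirms diagnosis; observes social behaviour, communication and general aspects; algorithm cut-offs for communication and reciprocal social interaction | No |
| CARS-BR | Classifies severity; 14 behaviour domains plus a general impression; overall score | No |

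The Discussion says the two measures will show whether the intervention affects ASD symptoms and their intensity. That is a symptom outcome.

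**Step 3. Count.** Constructs named: 2 (cognitive, behavioural). Instruments assigned: 2, the same for both. Instruments or subscores assigned to cognition alone: 0.

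**Step 4. Does the rationale point to a cognitive function that is tested?** The Introduction links the cerebellum to attention, decision making, language and affective regulation, and elsewhere mentions short-term and working memory. Section 2.3 lists no test of attention, memory or decision making.

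**Step 5. Is the site hypothesis stated consistently?** The Introduction confines motor-cortex effects to motor outcomes. Section 2.9 expects the motor effects to improve the participating children's global performance, including the cognitive and behavioural aspects on ADOS and CARS, and does not limit this to the cerebellar arm. The two statements differ.

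**Step 6. Illustration of precision for the site hypothesis.** This does not measure the construct problem. It shows only why the prediction of no effect needs an estimate with an interval. Assumptions: one comparison of two arms at a single time, equal SD, three arms of n, residual df = 3n − 3, and no baseline adjustment (which could narrow the interval).

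- Unadjusted 95% half-width in SD units: t(0.975, df) × √(2/n)
- Tukey half-width over three groups: q(0.95; 3, df)/√2 × √(2/n)

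| n per arm | df | Unadjusted | Tukey |
|---|---|---|---|
| 10 (30 recruited) | 27 | 2.052 × 0.447 = 0.92 | 3.506/1.414 × 0.447 = 1.11 |
| 8 (stated minimum) | 21 | 2.080 × 0.500 = 1.04 | 3.565/1.414 × 0.500 = 1.26 |

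Under these assumptions, a non-significant difference would be compatible with differences approaching a full SD or more.

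**The case against.** The strongest reply is that this is a matter of labelling in a disclosed secondary outcome. The article says openly that ADOS is a diagnostic tool put to a second use, and the Discussion already frames the inference as one about symptoms. Both facts stand, and they limit the seriousness of the point. They do not make ADOS a measure of cognition, and the aim, outcome list and hypothesis still use the word.

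A second reply is that the 14 CARS-BR domains are not listed, and that some of them, or the general aspects in ADOS, may touch on cognition. The documents cannot settle this. They do show that the domains are described as behaviour and that no cognitive score is defined.

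Three stronger readings are tempting but not supported:

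- **That a single severity score would serve as both outcomes.** There are two instruments, and both have domain scoring.
- **That the trial fails to separate cognitive from behavioural effects as it promised.** The terms are listed side by side, but the hypothesis and the measurement sections treat them jointly, and no contrast between them is planned.
- **That a non-significant motor-cortex result will be reported as no effect.** The hypothesis is worded as a belief, and neither section 2.5 nor any other section says non-significance will be read that way. Section 2.5 also plans Tukey comparisons among all three groups, so the direct cerebellum versus motor-cortex comparison is already available.

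Nor is this a detail that a condensed article leaves to the full protocol: the article states which instruments measure these aspects.

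**Conclusion.** The point holds in a limited form. Cognitive aspects are a named secondary outcome and part of the cerebellum-specific hypothesis, but only ADOS and CARS-BR are assigned to them, and the protocol describes both in terms of diagnosis, behaviour and symptom severity, with no cognitive score. As written, the trial can report a change in ASD symptoms; it has no basis for calling that change cognitive. This conclusion rests on the article's own descriptions of the instruments and on no numerical assumption.

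The site hypothesis should be tested by the direct difference between the active arms. The half-widths above illustrate why, under the simplifications stated there, and are not the size of the main problem. The Introduction and section 2.9 disagree on whether benefit beyond motor outcomes is expected only with cerebellar stimulation. The MABC-2 primary outcome and its sample-size basis are untouched. The change should be made because it alters what the trial may conclude at almost no cost.

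**What to change.** 1. In the objectives, the outcome list and the hypothesis, replace the cognitive and behavioural label with *ASD symptoms and symptom severity (ADOS, CARS-BR)*, and state that no conclusion on cognition will be drawn.
2. State that the site-specificity hypothesis will be assessed by the cerebellar-minus-motor-cortex difference in ADOS and CARS-BR change, with its confidence interval. This contrast is already within the planned Tukey comparisons. Significance in one arm beside non-significance in the other should not be used as evidence of specificity.
3. Reconcile the Introduction with section 2.9, so that both say the same about whether improvement on ADOS and CARS-BR is expected in the cerebellar arm alone or in the motor-cortex arm too.

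The cost is wording, with no new test, visit or participant. The downside is that the trial gives up a cognitive claim.

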## Ethics statement

The study was analyzed and approved by the Human Research Ethics Committee of Universidade Evangélica de Góias with the co-participation of the Follow Kids Child Neurorehabilitation Clinic (certificate number: 64474922.0.0000.5076). Written informed consent to participate in this study was provided by the participants’ legal guardian/next of kin.

## Abbreviations

ADOS: Autism Diagnostic Observation Schedule
ASD: Autism spectrum disorder
CARS-BR: Brazilian version of the Childhood Autism Rating Scale
DSM: Diagnostic and Statistical Manual of Mental Disorders
MABC: Movement Assessment Battery for Children
MEP: motor evoked potential
tDCS: transcranial direct current stimulation
TMS: Transcranial magnetic stimulation
TUG: Timed Up and Go
